#### Study execution

Participants obtain the internet information (EBPI or standard, respectively) on blood glucose disorders, metabolic testing (diabetes-testing) and prevention strategies. The survey is carried out at three points in time (T0/T1, T2), with the first two times during one visit to the website. T0 or T1 is the questioning before or after reading the information, so that the gain of knowledge and a characterisation of later drop-outs is ascertainable. T2 is the online follow-up survey two weeks after the first online session (see Figure 1).

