#### Randomisation

Randomisation takes place immediately before presentation of the information, deposited on a random number generator. To gain a balanced distribution of the study population characteristics, a stratified block randomisation is conducted (4 strata defined by women/men and 40-49 years/50 years and older, 1:1 randomisation between intervention and controls within each stratum using blocks of size 10).

Crossover between the study groups is not possible, because the IP-addresses of the participants are identified by the system.

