#### Statistical analysis

Data of all randomised participants excluding those with self-documented diabetes will be evaluated. The primary analysis will be performed on the study population of T1 compliers with non-missing primary outcome of knowledge. The secondary analysis set will be the subset of compliers of T1 and T2.

The persons who have prematurely terminated the study without completely documented knowledge outcome of T1 will be compared with the study population on the basis of the parameters which are assessed before randomisation (age, sex, education, life satisfaction, and pre-study knowledge about elevated blood glucose), using appropriate statistical tests (chi-square test, Fisher's exact test, t-test or Wilcoxon test). Furthermore, the subgroup of the T1/T2 compliers will be compared with the study population of T1 compliers in a similar manner.

Outcomes will be compared between intervention and control group on an 'intention to treat' basis. For the description of the population in terms of relevant basic parameters - according to distribution - frequency tables, prevalences with 95% confidence intervals or mean values with standard deviations will be calculated. Scores on knowledge and quality of the decision and satisfaction will be evaluated by average scale scores with standard deviations and percentiles. The estimates will be carried out in the intervention and control group respectively in total and stratified for relevant subgroups, e.g. age (40-49 years or older) and sex. To test any effects of the intervention, statistical comparisons will be performed - according to distribution - by chi-square or Fisher's exact test, t-test or Wilcoxon's rank sum test. The tests for each target variable is to be defined before the evaluation.

The primary outcome is an ordinal score with values 0-8. The distributions between intervention and control group will be compared primarily by Wilcoxon's rank sum test. In a secondary analysis the outcome "good knowledge" is defined by dichotomisation of the ordinal knowledge score using a predefined cut point of 5 (≥ 5 versus <5). Intervention and control group will be compared by chi-square test.

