The association between this primary outcome and predictors is estimated using multiple ordinal logistic regression models. A continuation-ratio logit model will be fitted [33]. To simplify the interpretation of the results the scale of the knowledge score will be reduced to 3 ordered values by the predefined classes 0-2, 3-5 and 6-8. The predictors are first examined by univariate models. Then, multiple models considering age, sex, socio-economic variables and participation in a blood glucose test will be discussed.

Then, multiple models considering age, sex, socio-economic variables, participation in a blood glucose test and pre-study knowledge about elevated blood glucose will be discussed. A final multiple regression model will be fitted.

A secondary analysis will be performed on the subpopulation of participants at T1 and T2 considering the ordinal outcomes "attitude" and "intention to undergo uptake a metabolic testing". These variables will be described non-parametrically and control and intervention group will be compared using Wilcoxon's rank sum test.

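### The only analysis set named for attitude and intention is those who also complete the two-week T2 survey, so a T1 comparison would lose T1 responders and be conditioned on a post-randomisation event

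*Protocol article*

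**What the plan says.** The Statistical analysis section of the protocol article defines two analysis sets. For knowledge: "The primary analysis will be performed on the study population of T1 compliers with non-missing primary outcome of knowledge". For the other: "The secondary analysis set will be the subset of compliers of T1 and T2". Later in the same section attitude and intention are assigned to the second set: "A secondary analysis will be performed on the subpopulation of participants at T1 and T2 considering the ordinal outcomes" attitude and intention, with the arms compared by Wilcoxon's rank sum test. The section also states a general principle: "Outcomes will be compared between intervention and control group on an 'intention to treat' basis".

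Timing comes from two other sections. Under Randomisation: "Randomisation takes place immediately before presentation of the information". Under Study execution: "T0 or T1 is the questioning before or after reading the information", both within one website visit, and "T2 is the online follow-up survey two weeks after the first online session".

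One check on T2 non-return is planned: "Furthermore, the subgroup of the T1/T2 compliers will be compared with the study population of T1 compliers in a similar manner". The manner referred to is a set of tests on variables recorded before randomisation (age, sex, education, life satisfaction and pre-study knowledge).

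**The concern.** Whether a participant comes back after two weeks is settled after allocation and after reading the material, so the material can influence it. Restricting a comparison to returners therefore compares selected groups, which need not be balanced in the way randomisation made the full groups balanced.

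For an effect measured at T1 this restriction is unnecessary. The answers are given in the same visit as the reading, before anyone can fail to return. Requiring T2 costs precision and opens a route to selection bias in the immediate effect of the information on attitude and intention. Knowledge at T1 carries no such requirement, so outcomes from the same visit would be reported on different populations.

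**Working it through.** **1. Order of events.** Randomisation, then reading, then T1 (same visit), then T2 two weeks later. T2 completion is a post-randomisation event. T1 completion is one too, but a much weaker condition because it only requires finishing the visit.

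**2. The plan's own figure.** Inputs from Sample size and statistical power: difference 0.20 SD, two-sided α = 5%, power 90%, equal groups.
- Normal approximation: n = 2 × (1.960 + 1.282)² / 0.20² = 526 per group after rounding up.
- t-test version: 526.3, so 527. The stated 527 reproduces.
- Power at 527 is 0.90. The figure thus contains no margin for T2 loss. It was set for knowledge, not for attitude or intention.

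**3. Precision lost by requiring T2.** The article gives no return rate, so r is an assumption, taken as equal in both arms. Standard error ratio = 1/√r. Power = Φ(0.20 × √(527r/2) − 1.96).

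| Assumed return r | n per arm | SE increase | Power for 0.20 SD |
|---|---|---|---|
| 100% | 527 | none | 0.90 |
| 80% | 422 | 12% | 0.83 |
| 60% | 316 | 29% | 0.71 |
| 50% | 264 | 41% | 0.63 |

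Worked line for 60%: 527 × 0.6 = 316.2; √(316.2/2) = 12.57; 0.20 × 12.57 − 1.96 = 0.555; Φ(0.555) = 0.71.

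**4. When selection biases the comparison.** Illustration with no true effect, a standard normal outcome, return following a logistic function of the outcome, and 527 T1 completers per arm. The mean among returners was found by numerical integration, and the type I error from a normal test of the difference in means. All return rates and slopes are assumptions.

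| Return by arm | Logit slope per SD, by arm | Bias (SD) | Type I error |
|---|---|---|---|
| 60% / 60% | 0.5 / 0.5 | 0 | 0.05 |
| 50% / 70% | 0.5 / 0.5 | 0.09 | 0.22 |
| 60% / 60% | 0.5 / 0 | 0.19 | 0.67 |

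Under no true effect, bias appears when return is related to the outcome and either the return rate or that relation differs between arms. In the third case it is about as large as the 0.20 SD the trial was sized on. In the first there is none.

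**5. Does the planned check cover this?** It compares returners with all T1 compliers, on pre-randomisation variables. No comparison of return between arms is stated. Similarity at baseline cannot show whether return depended on attitude or intention after reading, or did so differently by arm. The check describes the loss; it does not restore the randomised comparison.

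**The case against.** **The text does not say this is the sole analysis.** A reader might infer that the article rules out a T1 comparison in all T1 compliers. It does not. Its general statements, that data of all randomised participants without self-reported diabetes will be evaluated and that outcomes are compared by intention to treat, could cover attitude and intention. The dichotomised knowledge outcome is also called a secondary analysis without being tied to T2. This stands: the point is only that no other set is named for these two outcomes. The wording could also be read as each time point taken separately, but calling it a subpopulation, and defining the secondary set as compliers of both surveys, points to people who completed both.

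**Collection at T1 is inferred.** The instruments are not listed by time point and Figure 1 is not shown. If attitude and intention were asked only at T2, no T1 data would be lost and the table of precision losses would not apply. If the aim is the course from T1 to T2, a paired set is a natural choice. Both stand as limits.

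**T2 loss was anticipated.** Returners are to be compared with T1 compliers, and quit points are recorded for a drop-out analysis. That is fair credit, but it does not remove the problem (step 5).

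**The primary set is itself conditioned on completion.** True, but only within a single visit. Requiring T2 adds a further condition that a T1 measurement does not need.

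**Conclusion.** The point holds in conditional form. As written, the only set named for attitude and intention is completers of T1 and T2. If these outcomes are collected at T1, that rule drops usable T1 responses, conditions the T1 comparison on a post-randomisation event, and sits poorly with the intention-to-treat statement.

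The size depends on a return rate the article does not give: a standard error 12% to 41% larger for assumed return of 80% down to 50%.

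Two stronger conclusions are not supported. One is that the results for attitude and intention will be biased: the article gives no information on how return relates to arm or outcome, and the illustration includes a case with no bias. The other is that these analyses miss a power target: none is stated for them, and the 90% belongs to knowledge. The primary test and the 527 per group are untouched. The change is nonetheless worth making, because the better analysis set is already defined for the primary outcome.

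**What to change.** - State at which time points attitude and intention are collected.
- If they are collected at T1, compare them between arms at T1 in all eligible T1 compliers with non-missing data for the outcome, on the same principle as the primary set.
- For T2, report return by arm and add an analysis that uses the available T0 and T1 data under a stated missing-data assumption. Multiple imputation and a repeated-measures ordinal model that retains T1-only participants are both reasonable; neither is the only option.
- Keep the Wilcoxon test in T1/T2 compliers as a sensitivity analysis, and align the wording with the intention-to-treat sentence.

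The cost is revised wording and one additional analysis; no new data are needed if the items are asked at T1. The T2 analysis would rest on a missing-at-random assumption that the data cannot verify, which should be said openly.

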#### Sample size and statistical power

The main outcome is knowledge, on which the sample size calculation is based. The knowledge questionnaire includes 8 items. Each item is rated right/wrong or not completed, which will be awarded with 0 or 1 point. Result of the knowledge test therefore cover 0-8 points. The statistical power using primarily Wilcoxon's rank sum test was estimated roughly using the power calculation of the corresponding t-test assuming approximate normal distribution. Nothing was known about the distribution of the ordinal outcome. A sample size of 527 evaluable participants per group will be enough to detect a difference of 0.20 σ of the expected values between intervention and control group by 90% power using a significance level of α = 5% and a 2-sided test (σ = common standard deviation on both groups). In view of the planned multiple regression analysis and the secondary analysis of the ordinal outcome a relatively large sample size was planned.

#### Ethical considerations

Participation is based on informed consent in accordance with the Declaration of Helsinki. All participants give their informed consent for participation in the study in an internet formulary.

The data security official of the German Diabetes Centre approved the study on 16/01/2008 and the amended protocol on 02/08/2009.

The Ethics Committee of the University of Düsseldorf approved the design of the study on 28/02/2008 and the amended protocol on 07/08/2009, reference number: 3020.

## Discussion

Diabetes prevention is currently being widely discussed. An evidence-based processing of the available evidence is therefore of great relevance and can be widely used.

In health services research patient-oriented questions and information transfer, information presentation and evaluation are increasingly playing a central role [34]. Thus, a thorough review of the project outcomes is of great interest, also from a scientific perspective.

Health information is increasingly available on the internet. An online information is therefore of major practical importance [35]. With the initial establishment of an evidence-based information to a "pre-diabetic" situation and primary prevention of diabetes and its use as an online-based evidence-based information, the project is also from a international scientific point of view a methodological challenge and markedly innovative. Web-based systems are not likely to achieve representative results for the population. Potential advantages lie in new opportunities for evaluation and possibly in a high cost effectiveness of the method. The design of this study may act as prototype for other web-based prevention information and their evaluation. Concerning potential long-term consequences of the intervention, no statements are possible at this time.
